**Figure 2 F2:**
[figure not shown]
Scheme of potential contamination. The potential contamination in a hospital, in and between wards, physicians and patients

The stepped-wedge design, which involves the randomised and sequential rollout of the intervention to clusters over time, was chosen because it can model and adjust for underlying temporal trends and results in all clusters having access to the intervention at the end of the rollout period which seems desirable from an AMS perspective.^13^

### Study population

In our study, the intervention will be targeted at physicians that prescribe antimicrobials. To avoid possible contamination, the prescribers will be randomised at the ward/specialty level and not individually (see above). Process parameters will be determined in physicians who have been randomised to use the app as per the process indicated above. Outcome parameters such as appropriate antimicrobial use will be determined at the patient level at participating wards (control and intervention) who meet the following criteria: being a medical or surgical specialty patient at least 18 years of age for whom antimicrobial drugs are prescribed.

### Intervention

The Spectrum app, available for iOS and Android and on the web, has been developed in Canada (www.spectrum.app) and is now being used in over 50 hospitals, mainly in Canada and the USA. The app has been developed with the help of human factor experts and integrates multiple resources into a unified user-friendly interface for use at point-of-care to improve antimicrobial prescribing (figure 3).

**Figure 3 F3:**
[figure not shown]
Interface of the AB-assistant app. On the left the Home screen is shown. In the middle checkboxes are shown to guide the user to the correct therapy for Meningitis. The right screen shows details about Amoxicillin-Clavulanate regarding dosing and general spectrum of activity.

For the purpose of this study the app and the content management system were extended to also support languages other than English (French, Dutch and Swedish) and will be used for prescribing guidelines, pathogens, antimicrobial drugs and antibiograms. App content such as local guidelines, information regarding antimicrobial drugs, and micro-organisms of each hospital was entered by investigators of the Dutch, Swiss and Swedish hospitals (RH, GC, BH and [name]). App content is identical to content of the local guidelines if these are published on a website. Minor discrepancies may occur if the local guidelines are published in a digital document (ie, PDF) or on paper. The app can be more up to date in those cases.

The allocation of the timing to introduce the app will be concealed to the participating cluster up until 2 weeks before initiating use of the intervention. At the start of the intervention physicians on the intervention ward(s) will be informed about the function and content of the app. During the trial, only physicians on the intervention wards will be whitelisted to be able to use the app. Access to the app will be centrally withdrawn if a physician leaves the intervention ward (eg, to work on a different (ie, non-intervention) ward). The conventional route of guidelines (eg, portable document formats (PDF), website or printed booklet) will still be available at all times. Physicians can freely choose between the app and the conventional route. Physicians on control wards will only be able to access the guidelines using the conventional route.

### Patient and public involvement

No patients or public have been included in the study design.

## Outcome parameters

Outcome parameters (table 3) will be monitored using a digital case report form (CRF) (online supplementary appendix 1) in the software application OpenClinica.^14^

10.1136/bmjopen-2019-033640.supp1Supplementary data

**Table 3 T3:** Secondary study parameters/endpoints and other study parameters

Outcome type	Examples	Data source
Quantitative antimicrobial use	Total prescription of antimicrobial drugs1 in DDD/admission, DDD/PD, DOT/PD and DOT/admission	EHR
	Total prescription of broad spectrum and restricted antimicrobial drugs in DDD/admission	Administrative data
	Total prescription of antimicrobial drugs per AWaRe category^19^ in DDD/admission	
	Antimicrobial costs	
Patient	Length of hospital stay	EHR
Related	In hospital mortality within 30 days after admission (all cause)	Administrative data
	Unplanned hospital readmissions within 30 days after discharge	
	Transfer to intermediate care or ICU within 30 days after admission	
Microbiologic and HAI	Incidence of healthcare facility onset *Clostridium difficile*	EHR
	Incidence clinical cultures with multi-drug resistant organisms (MRSA, ESBL-E, CPE, VRE, multidrug resistant *Pseudomonas aeruginosa*) denominated per 1000 PD and admission	Microbiology database
		Infection control surveillance data
Physician related	Uptake of the AB-assistant (total users and number of sessions per user, time spent per session, time spent per screen, number of times each screen is viewed)	Content Management System
	Differences in uptake between centres	Content Management System
	Actual use of app and experiences while using it	Survey
Other outcomes	Number of infectious diseases consultations	EHR

1. Antimicrobials belonging to Anatomical Therapeutic Chemical Classification System class J01, J02, J03, J04, J05 (excluding anti-HIV drugs), P01, P02 and P03, oral vancomycin (A07AA09) and fidaxomicin (A07AA12).

AWaRe, access, watch, reserve; CMS, content management system; CPE, carbapenemase-producing enterobacteriaceae; CRE, carbapenem-resistant enterobacteriaceae; DDD, defined daily dose; DOT, days of therapy; EHR, electronic health record; ESBL-E, extended-spectrum beta-lactamase-producing E; HAI, hospital acquired infections; ICU, intensive care unit; MRSA, methicillin resistant staphylococcus aureus; PD, patient-days.

### Primary outcome parameter

Appropriateness of empiric antimicrobial therapy expressed as number and percentage of appropriate treatment episodes compared with all assessed treatment episodes.

Definitions for the primary outcome are:

Antimicrobial drugs assessed are anatomical therapeutic chemical (ATC) classes J01, J02, J03, J04, J05 (excluding anti-HIV drugs), P01, P02 and P03.Treatment episodes are defined as the duration of treatment given for a specific infectious episode with gaps of treatment of no longer than 1 day.Treatments are antimicrobials started during the measurement period at the participating entity. If a treatment was started within 24 hours before transfer in the emergency room or other ward and has not been changed during the first 24 hours stay at the ward, the treatment will be considered in accordance with the choice of the ward physician.Treatments are in patients either newly admitted to the participating entities or already hospitalised during the preintervention period.Appropriateness of empiric therapy includes choice, route and the dose of the antimicrobial drugs.Appropriateness of therapy is in concordance with local treatment guidelines. If no guidelines are available, or if the treatment deviates from the guidelines or if treatment is guideline concordant but treatment should have deviated from the guideline (eg, because of allergies, colonisation with multidrug-resistant bacteria, other microbiological results, interactions, comorbidities or recent exposure to antimicrobials), anonymised cases will be discussed between two independent local infectious disease (ID) physicians. If they do not agree a third independent local ID physician will be consulted to adjudicate.For each patient only the first treatment episode during the measurement period will be evaluated. For patients treated for >1 infection (eg, pneumonia and *C. difficile* infection) appropriateness will be assessed for all infections combined (eg, if treatment is appropriate for *C. difficile* infection but inappropriate for pneumonia the treatment would be categorised as inappropriate).

### Secondary outcome parameters

Total prescription of antimicrobial drugs on the cluster-level expressed as defined daily dose (DDD) and day of therapy (DOT) denominated by patient-days and admission; subcategories by type of antimicrobial (antibiotic, antifungal, etc), WHO Access, Watch, Reserve (AWaRe) categories and restricted antimicrobial drugs (table 3).Clinical secondary outcomes: length of hospital stay, in hospital mortality and readmissions within 30 days after discharge, incidence/prevalence of key antimicrobial resistant (AMR) pathogens such as *C. difficile*.Process parameters of the intervention: penetration of the AB-assistant (total users and number of use of app), and uptake differences between centres.

Along side the randomised controlled trial (RCT), an uptake analysis will be performed to assess actual use of the app as well as an evaluation of use.

### Uptake analysis

A number of parameters regarding use of the app will be collected and made available on a secure dashboard to authorised users at each site. These include number of monthly users and monthly sessions, number of times each antimicrobial, pathogen or clinical pathway screen is viewed, use by hospital, department and medical specialism. These data will enable in-app behaviour to be correlated with actual prescribing behaviour on ward level and site-wide basis, thereby strengthening the association of the intervention to observed outcomes.

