### Study design

We plan to conduct an international, multicentre, stepped-wedge cluster randomised trial to assess whether making a smartphone app for AMS (Spectrum) can improve the appropriateness of antimicrobial prescribing in hospitalised patients. Table 2 illustrates the study question according to the Population, Intervention, Comparator, Outcome and Time (PICOT) framework.

**Table 2 T2:** PICOT of the study question

Population	Physicians involved in antimicrobial prescribing decisions for hospitalised adult patients in the participating centres
Intervention	Making a smartphone application with antimicrobial treatment recommendations available to physicians mentioned above
Comparator	Standard-of-care antimicrobial stewardship
Outcome	Appropriateness of empiric antimicrobial prescribing based on predefined criteria
Time	12 months consisting of a 6 months introduction period with 6 months follow-up to assess sustainability

In total, 36 medical and surgical entities (defined as wards (Sweden) or specialties (Switzerland, The Netherlands) will be included in the study using a stepwise design with six entities (two entities per participating hospital) 4-weekly at six introduction moments (figure 1). The primary outcome is appropriateness of empiric antimicrobial prescriptions assessed prior to implementation and up to 12 months after the intervention (after 6 months free use of the app). Empiric therapy is defined as^1^ treatment started based on clinical evaluation before culture results are known,^2^ the duration of treatment is longer than 24 hours (from the moment of prescription) and^3^ the treatment is not specifically recorded as prophylactic. Initial targeted therapy for which there is a local guideline available (eg, *Clostridium difficile*) may be assessed for appropriateness.

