**Figure 1 F1:**
[figure not shown]
Study design. In all time periods (total of 7) there is an uptake period of 2 days and a measure period of 26 days. During the baseline period only a measure period of 2 weeks will be performed.

The entities will be randomised as to the time period of making the app available (see the Intervention section). The order of implementation will be determined by a computer-generated list of random numbers programmed by a statistician otherwise not involved in the trial and AMS activities. Randomisation will be stratified by the type of specialty (medicine, surgery, etc). After a baseline period of 2-week measurements, six periods of 4 weeks will follow in which the intervention is introduced in six entities (in three hospitals) until all entities have implemented the intervention. We plan to include 36 entities in total (see sample size calculation below) during the six introduction moments and at the end of the inclusion time we will allow the use of the app by everyone, also wards/specialties not included in the study. In this way, the trend in appropriate antimicrobial use can be monitored per ward/specialty and the decrease of antimicrobial use and appropriateness of empirical antimicrobial therapy can be followed during the stepwise implementation.^12^ At 12 months (after 6 months free use of the app) we will have a 2-week measurement period to evaluate the sustainability of the intervention. The study will start between February 2020 and June 2020, and end 12 months later.

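### The planned site-wide correlation of app use with prescribing cannot support attribution to the app, because the rollout makes site-wide use follow calendar time

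*Protocol article*

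**What the plan says.** The Uptake analysis section lists the usage measures to be collected, among them "number of monthly users and monthly sessions". It then says: "These data will enable in-app behaviour to be correlated with actual prescribing behaviour on ward level and site-wide basis", and gives the purpose as "thereby strengthening the association of the intervention to observed outcomes".

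Other sections fix how use can vary:

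- **Study design:** the app is introduced "with six entities (two entities per participating hospital) 4-weekly at six introduction moments", and this continues "until all entities have implemented the intervention".
- **Intervention:** during the trial "only physicians on the intervention wards will be whitelisted to be able to use the app", so use before crossover is zero by design. After crossover use is optional: "Physicians can freely choose between the app and the conventional route".
- **Justification of the stepped-wedge design:** the design was chosen partly "because it can model and adjust for underlying temporal trends".
- **Statistical methods:** the outcome models carry time period as a fixed effect. The article does not say whether the uptake correlation does.

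**The concern.** The design rationale recognises that prescribing may drift over time and that the drift must be separated from the effect of the app. The uptake analysis brings the problem back. Site-wide use is zero at baseline and is built to grow with each step, so it rises together with anything else that rises over the same months. An improving background trend in appropriateness would then appear as a positive association between use and outcome, whether or not the app works.

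What is at stake is interpretation. The protocol itself notes that high baseline appropriateness in these hospitals may raise the risk of a negative trial. If the primary result were null or borderline, a positive use-outcome correlation could be offered as corroboration on the strength of this sentence, when a trend alone could have produced it.

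**Working it through.** The protocol gives no figure for this analysis, so there is none to reproduce.

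**Inputs from the protocol.** 36 entities, 12 per hospital; 7 periods; 6 steps with 2 entities per hospital at each; 15 patients per entity-period; intra-entity correlation 0.1; baseline appropriateness 60%, target 70%.

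**Assumptions.** The app has no effect. Appropriateness drifts linearly by D over the rollout, with D = 3, 5 or 10 points up, or 5 or 10 points down. Use after crossover is random and unrelated to outcome. Site-wide means one site's aggregate use against its mean appropriateness over the 7 periods.

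**Step 1: exposure against calendar time.** Number the periods t = 0 to 6. The exposed share at each site is t/6: 0, 17, 33, 50, 67, 83, 100%. This is linear in t, so its correlation with period is 1.0.

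For single ward-periods the exposure indicator X has mean 0.5 and SD 0.5, and t has mean 3 and SD 2. E[Xt] = (1/6) × mean(t²) = (1/6) × (91/7) = 2.167. The covariance is 2.167 − 0.5 × 3 = 0.667, and r = 0.667 / (0.5 × 2) = 0.67.

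**Step 2: site-wide correlation with a useless app, by hand.** The trend has SD 2 × D/6 = D/3 across periods. A site mean rests on 12 × 15 = 180 patients. Entity effects are constant over time and drop out, so the sampling variance is about 0.9 × 0.65 × 0.35 / 180 = 0.00114. Hence r ≈ (D/3) / √(D²/9 + 0.00114):

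- D = 0.03: 0.0100 / √0.00124 = 0.28
- D = 0.05: 0.0167 / √0.00142 = 0.44
- D = 0.10: 0.0333 / √0.00225 = 0.70

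**Step 3: simulation with no app effect.** Mean correlations over 2,000 runs per trend, 36 entities:

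| Trend over rollout (points) | Site-wide | Ward-period, pooled | Within ward | Adjusted for ward and period |
|---|---|---|---|---|
| 0 | 0.01 | 0.00 | 0.00 | 0.00 |
| +3 | 0.28 | 0.03 | 0.05 | 0.00 |
| +5 | 0.44 | 0.05 | 0.09 | 0.00 |
| +10 | 0.71 | 0.10 | 0.18 | 0.00 |
| −5 | −0.43 | −0.05 | −0.09 | 0.00 |
| −10 | −0.70 | −0.10 | −0.17 | 0.00 |

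With other random seeds and a Poisson distribution of sessions, the site-wide means are 0.28–0.29, 0.44–0.46 and 0.73 for rises of 3, 5 and 10 points, and the within-ward values reach about 0.2.

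**Step 4: how often it would look significant.** For one hospital with 7 points, two-sided 5% significance needs |r| > 0.754. With a useless app the site-wide correlation is significantly positive in about 9%, 18% and 55% of trials for rises of 3, 5 and 10 points, against a nominal 2.5%. A linear model for use with entity, period and exposure terms brings this back to 2.4–2.9%.

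**Step 5: what adjustment leaves.** At ward level, adjustment removes the time-induced part, and the remaining information is how much physicians chose to use the app. Site-wide, the exposed share is the same function of period in all three hospitals, so period adjustment leaves no designed contrast.

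**The case against.** The strongest reply is that the sentence is a short rationale for collecting dashboard data. It names no estimator and does not say that the correlation is unadjusted, and a full analysis plan, not shown here, may specify adjustment. This stands as far as the ward-level model goes, and the absence of that model from an article is not a fault. It does not rescue the site-wide correlation, for which period adjustment leaves no designed contrast, nor the inference, which the article itself states.

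Three stronger readings are tempting, and the documents do not support them:

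- *Any secular trend would favour the app.* Only an improving trend does. A worsening one pushes the correlation against it.
- *Calendar time is the only source of variation in use.* Use is voluntary, and differences in uptake between centres are a planned process measure, so wards and sites can differ within the same period. Such comparisons are not confounded by time. Their weakness is that intensity of use is not randomised.
- *The trial's main result is compromised.* The uptake analysis runs beside the randomised comparison, whose model includes period effects.

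It is also fair to say that the size depends on the trend. The 55% figure needs a background rise as large as the whole target effect, and with a 3-point rise about 91% of trials would show no significant positive correlation. The section also collects screen-level views, which could support other analyses than the one simulated here.

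**Conclusion.** The point holds in a limited form. The site-wide correlation carries no evidence about the app that can be separated from calendar time. With a useless app, its mean is about 0.3, 0.45 and 0.7 for assumed improvements of 3, 5 and 10 points. The ward-level version is biased only slightly by time, and adjustment removes that bias. The adjusted association is still observational, so it does not strengthen attribution beyond the randomised contrast. The correlation of 1.0 between exposed share and period follows from the schedule alone. The other sizes rest on the assumed linear trends and use distributions. This is a minor point about interpretation and does not alter the primary analysis.

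**What to change.** In the Uptake analysis section:

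1. Do not use the site-wide correlation as evidence of effect. Site-wide use can still be reported descriptively.
2. Estimate the ward-level association between use and appropriateness within entities, adjusted for period and exposure status.
3. Label that association exploratory and non-randomised.
4. Remove or soften the clause claiming that it strengthens the link between intervention and outcomes.

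This takes a reworded sentence and one model in place of a correlation, with no new data. The downside is a less favourable reading of the uptake data.

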## Evaluation of use

Insufficient user friendliness and lack of integration into the workflow are key impediments to the uptake of IT-based AMS interventions. Therefore, we will evaluate the physicians’ experiences with the use of the app. After each introduction period all physicians of intervention wards will receive a questionnaire to collect information on experiences using the app. The questionnaire will be based on information from the literature,^15^ see online supplementary appendix 2.

10.1136/bmjopen-2019-033640.supp2Supplementary data

## Blinding during evaluation of outcome parameters

Given the nature of the intervention and the primary outcome assessed it will be difficult to blind the outcome assessor. To assure that assessment bias is limited we will have a subset of outcomes (10%) assessed by an independent investigator blinded to the study period.

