## Introduction

Antimicrobial drugs are an indispensable part of modern medicine, which depends on effective drugs for prophylaxis and treatment. Yet, only around 40%–70% of empiric antimicrobial regimens are considered appropriate with regard to their indication, the choice of agent, dosing or duration.^1–4^ Inappropriate antimicrobial use enhances the risks of treatment failure and side effects in the individual patient, and accelerates selection and transmission of antimicrobial-resistant pathogens in healthcare settings and the community.^5^ Many antimicrobial stewardship (AMS) interventions have been shown to increase appropriateness of antimicrobial drug prescribing.^6^

A software application (app), which is compatible with mobile electronic devices such as smartphones and tablets, and increases the availability of existing national and local antibiotic guidelines plus local antibiograms, may improve antimicrobial prescribing, reduce medication errors and ultimately improve patient outcome. Due to its highly customisable nature, a digital app has the potential to become an effective AMS tool in all countries.

Mobile-software apps seem particularly interesting for the purpose of AMS, since they do not require access to electronic health records (EHRs) or computerised physician order entry systems, that are costly, difficult to maintain and not easily customisable. Most healthcare workers own a smartphone and often use it to access information to assist in their treatment decisions.^7 8^ The vast majority of available apps developed to support prescription of medicines are limited to knowledge content and do not provide decision support algorithms. Further, they have rarely been evaluated in clinical trials.^9^ To date, most reported digital AMS interventions are single-centre studies with limited internal validity due to methodological limitations and uncertain external validity.^4 10 11^

In the present study, we will evaluate the implementation and impact of a smartphone-based software app (the AB-Assistant, Spectrum, Calgary, Canada) adapted to local conditions in an international clinical trial using a stepped-wedge cluster randomised design and appropriateness of empiric antimicrobial prescribing as the primary outcome.

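### The judgement-based primary outcome is scored unblinded except for a 10% subset, although cases for the infectious disease panel are already anonymised and could be masked to ward, date and period at low cost

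*Protocol article*

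**What the plan says.** The primary outcome is defined in the protocol article, under Primary outcome parameter, as "Appropriateness of empiric antimicrobial therapy expressed as number and percentage of appropriate treatment episodes compared with all assessed treatment episodes". Scoring starts from concordance with the local guideline, but three kinds of case leave that rule: those with no guideline, those that deviate from it, and those where it was followed but should not have been. For these, "anonymised cases will be discussed between two independent local infectious disease (ID) physicians", and "If they do not agree a third independent local ID physician will be consulted to adjudicate".

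On masking, the section Blinding during evaluation of outcome parameters says: "Given the nature of the intervention and the primary outcome assessed it will be difficult to blind the outcome assessor". The remedy is that "we will have a subset of outcomes (10%) assessed by an independent investigator blinded to the study period". The article does not say that the remaining 90% is scored blind. It also does not say whether anonymising a case for the panel removes the ward, the date or the period.

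Under Statistical methods, the primary model has time period and treatment as fixed effects and entity as a random effect.

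**The concern.** Two steps in the scoring call for judgement. One is the panel's decision whether a deviating or no-guideline case was nevertheless appropriate. The other is the earlier decision to refer a concordant case at all, that is, "if treatment is guideline concordant but treatment should have deviated from the guideline". The app is meant to raise guideline adherence, so someone who knows that an entity already has it may read borderline cases differently.

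In this stepped wedge every entity contributes both control and app periods, so entity and calendar date together reveal allocation. If judgement shifts with known app status, the shift enters the treatment coefficient and nothing in the data separates it from a real effect.

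The stated reason for leaving the assessor unblinded is also weak on the article's own terms. If one investigator can score 10% of outcomes without knowing the period, the nature of the intervention does not prevent it.

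**Working it through.** **1. Share of episodes that depend on judgement.** The referral rule under Primary outcome parameter, cut short here, begins: "If no guidelines are available, or if the treatment deviates from the guidelines or if treatment is guideline concordant but treatment should have deviated from". An inappropriate episode must fall into one of these three groups, so the judged share is at least 1 − (share appropriate). The Sample size section plans for 60% rising to 70%.
- Judged share ≥ 1 − 0.70 = 30% to 1 − 0.60 = 40%.
- 24 entities: 24 × 7 × 15 = 2,520 episodes, of which 756 to 1,008 are judged.
- 36 entities: 36 × 7 × 15 = 3,780 episodes, of which 1,134 to 1,512 are judged.

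This is a lower bound, because cases that the panel rules appropriate are judged too.

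**2. Reach of the blinded subset.** 10% is 252 of 2,520 or 378 of 3,780. That leaves 2,268 or 3,402 episodes without a blinded assessment.

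**3. The plan's own power figure.** Stated: 81% with 24 entities, 7 periods, 15 patients per entity-period and an intra-entity correlation of 0.1. I used the Hussey–Hughes stepped-wedge variance with 4 entities per step, 6 steps, within-entity variance 0.6 × 0.4 = 0.24 and between-entity variance 0.24 × 0.1/0.9 = 0.0267. This gives SE = 3.37 points. A two-sided 5% t test on 22 df then has 81.0% power for 10 points. Neither alpha nor the t reference is stated in the article; normal approximations with equal periods give 84–90%. With 36 entities the same formula gives SE = 2.75 points.

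**4. Which leniency biases the result.** Write the scored outcome as truth plus a scoring shift.
- A shift common to all entities in a calendar period goes into the fixed period effects and largely leaves the treatment estimate.
- A shift applied to entities that have the app, within the same period, is aligned with the treatment term. It adds (judged share) × (net leniency) to the effect.

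**5. Size under assumed leniency.** The documents give no leniency figure. I assume net shifts of 2.5, 5 and 10 percentage points of judged cases, with 40% judged. False effect = 0.40 × shift. Type I error is the probability that |T| exceeds its 5% critical value, where T is non-central t with non-centrality (false effect)/SE and 22 or 34 df.

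| Assumed shift in judged cases | False effect | Type I error, 24 entities | Type I error, 36 entities |
|---|---|---|---|
| 2.5 points | 1 point | 6% | 6% |
| 5 points | 2 points | 9% | 11% |
| 10 points | 4 points | 21% | 29% |

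With 30% judged, the same shifts give false effects of 0.75, 1.5 and 3 points, and type I error of about 6%, 7% and 14% (24 entities) or 6%, 8% and 19% (36 entities). A downward shift would instead hide a real effect. The calculation uses one model for all centres, whereas the planned primary analysis is by centre and then combined, so the figures are indicative.

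**6. What the re-read can detect.** Exposed and unexposed entity-periods are equal in number (21 of 42 cells in the 6 × 7 layout), so the subset splits about 126/126 or 189/189. With an assumed discordance d between the two readings, the 95% half-width for the difference in net reclassification is 1.96 × √(d × 2/n per arm).
- 126 per arm: 5.5 points at d = 5%, 7.8 points at d = 10%.
- 189 per arm: 4.5 points at d = 5%, 6.4 points at d = 10%.

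So the subset could not rule out a bias of 2 to 4 points.

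**The case against.** The other side has real substance.

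- **Safeguards exist.** Scoring is anchored to written local guidelines, judged cases get two independent readers and a third to adjudicate, and the limitation is disclosed. Nothing is concealed or miscalculated. This stands, and it lowers the severity.
- **The article does not say the panel knows the period.** A reader might infer that the ID physicians see ward and date. The text does not establish this: it calls the cases anonymised and is silent on those fields, and a fuller document may specify the extract. What the article does fix is that the assessor is not blinded beyond the 10%.
- **Time adjustment protects against part of the problem.** A reader might infer that any drift in leniency over time moves the primary result. It does not, because the period effects absorb what is common to a period. Bias needs leniency linked to which entities have the app.
- **Leniency is assumed.** A reader might take roughly 30% false positives as the expected consequence. That figure belongs only to the largest shift tabulated, with 40% judged and 36 entities. Smaller shifts leave the error near 6–11%, and the sign is unknown.
- **Masking is not free or complete.** The decision to refer a concordant case draws on allergies, colonisation, interactions and other details taken from a dated record, so masking it may mean separating the person who extracts from the person who scores. Local ID physicians do consultations and ward rounds (Table 1) and may recognise cases. The Introduction's remark that with mobile apps "they do not require access to electronic health records (EHRs") does not settle what an assessor knows. This supports the word difficult, but not leaving the panel cases unmasked.

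**Conclusion.** The concern holds in a limited form. The article leaves a partly subjective primary outcome unblinded for 90% of episodes, on a ground that its own blinded subset undercuts, and it already prepares anonymised cases on which masking could be applied. At least about 30–40% of episodes pass through judgement, assuming the referral rule is followed and the planned appropriateness levels hold. Leniency tied to known app status would be indistinguishable from the treatment effect. The illustrated false effects of 1 to 4 points against the 10-point target rest on assumed shifts in either direction; they show sensitivity and do not predict bias. The 10% subset can raise an alarm but leaves the primary result as it is. Severity: should fix, as a cheap improvement to a disclosed weakness.

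**What to change.** State that every case going to the ID physicians is presented without entity, calendar date or study period, with dates shown as days relative to the start of treatment, and that each review batch mixes control and app periods. Where existing staff allow, make the decision to refer a guideline-concordant case on the same masked extract, or replace it with a prespecified list of triggers. Keep the 10% blinded re-read as a check of agreement.

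The panel part needs no added assessors and no change to endpoint, sample size or intervention. The costs are preparing the extracts, later scoring because of batching, and possibly separating extraction from scoring at the referral step. Masking will remain imperfect where a local physician recognises a case. It must be in place before scoring begins.
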